**Intervention study design**

The study will be a **cluster randomized intervention trial,** with **cross-over design** carried out in three phases:

(1) a 3 month screening reinforcement phase during which the adherence to the admission and discharge MRSA screening protocols will be promoted and monitored monthly to achieve > 80 % compliance rate, application of isolation precautions to MRSA colonized patients will be measured and checked to achieve > 80 % compliance and the MRSA acquisition rate will be checked to lie within 95 % confidence limits of the projected 3% estimate. In addition, the length of stay per ward will be measured and checked for homogeneous distributions.

(2) a 5 month conventional detection test (standard care) phase during which MRSA screening will be performed by optimized conventional culture methods 6 days a week during working hours.

(3) a 5 month rapid detection test intervention phase during which admission MRSA screening will be performed by rapid PCR testing 7 days a week during working hours.

After eligible wards in each hospital have been checked to meet these inclusion criteria in phase (1), the sequential order of inclusion of eligible study wards in phase (2) and (3) will be randomly assigned within each centre by assigning a number to each ward and using a computer generated list of random numbers per study arm in each hospital so that one half of the wards will start phase (2) for the first 5 months and then phase (3) for the following 5 months whereas the other study wards will be “crossed-over” to follow the reverse sequence. No wash-out period will be used between phase (2) and (3). If the analysis of patient length of stay by ward indicates homogeneous distribution with markedly different median values between wards, stratified randomisation of wards within short/long (below/above pooled median) stay groups will be considered.

The planned study start date is: November 3rd, 2008 for the baseline observation and completion is planned on December 31st, 2009 (post-poned to end January, 2010 see addendum).

Admission screening: evaluation of patient sampling procedures:

During the entire study period (baseline and intervention phase), the infection control nurse responsible for the study will perform daily rounds in each of the study wards to ensure that screening of all newly admitted patients is being done systematically and without delay.

In addition, during a defined period, he or she will collect individual patient data on a subset of 20 % of included patients to identify risk factors for MRSA carriage based on history taking (notion of previously recorded MRSA carriage, transfer from other department or hospital, transfer from a nursing home, hospital stay in the previous year, attending outpatient care at a clinic in the previous year, presence of chronic skin sores, or living/working in a livestock farm, working as veterinarian or in a slaughterhouse). These data will be analysed to estimate the predictive value of these risk factors for the carriage of MRSA.

In the control arm, as per routine infection control policy in each institution, all patients admitted to study wards and presenting with will be sampled within 24 h after admission by taking swabs of anterior nares, throat, perineum and of any wounds, bladder catheter or intravenous catheter exit site (see appendix 1 for conventional MRSA screening procedures). Patients with previously recorded active MRSA carriage will be presumptively placed in contact isolation until three new series of conventional selective cultures of relevant body sites are found negative.

In the rapid test intervention arm, all patients admitted to study wards will be sampled within 24 h after admission. To ensure comparison of like with like, sample taking will include: (1) a swab from the anterior nares for PCR testing according to the test manufacturer’s instructions (see appendix 2 for rapid PCR screening test procedure); (2) the swab of anterior nares, and swabs from throat, perineum and of any wounds, bladder catheter or intravenous catheter exit site will be processed by conventional testing (see appendix 1 for conventional MRSA screening procedures). Patients with previously recorded active MRSA carriage will not be sampled for PCR testing but placed in pre-emptive isolation until three series of conventional selective cultures of relevant body sites are found negative.

Thus, patients in each arm will be managed identically, except that the rapid PCR test will be performed and its results made immediately available to infection control and clinical staff in the intervention arm.

MRSA isolates will be tested for mupirocin susceptibility and stored at -80°C for genotyping.

Additional contact isolation precautions.

MRSA contact isolation precautions will be applied to hospitalised patients as per local policy (see appendix 3 for isolation procedures in HE and AZSJ hospitals) either when previously recorded in the laboratory information file as active MRSA carrier or as soon as newly detected by either culture or PCR. Patients will be released from isolation after three consecutive culture screens for MRSA are negative after the end of therapy. Topical decolonisation therapy will be applied as per routine protocol in each institution (see appendix 4 for decolonisation procedures in HE and AZSJ hospitals) to all patients with either a positive MRSA culture and/or PCR.

Notification of screening results and process time recording.

Results of MRSA screening tests will be notified electronically to clinicians by either the technologist or biologist on duty through the laboratory information system (LIS) as well as with a telephone call to the Infection Control study nurse (during working hours) or the unit head nurse (outwith working hours). For culture tests, both presumptive positive results based on colony pigmentation typical for MRSA on chromogenic selective culture medium as well confirmed identification results will be notified immediately by the same communication modes. The precise timing (date, hour, min) of all telephonic result notifications will be recorded in the LIS.

The date and time (hour; min) of patient admission to study ward, as well as of patient placement in contact isolation or release from isolation will be recorded by the infection control study nurse. The date and time (hour; min) of screening sample reception in the laboratory, as well as of result electronic notification will be recorded by the LIS.

Primary outcome monitoring and case finding procedures.

To monitor MRSA acquisition for primary endpoint measurement, active discharge surveillance will be performed in all patients who have stayed in study wards for more than 48 h by collecting surveillance cultures for MRSA either on the day of being discharged or within 72 h prior to discharge from the study ward. Discharge surveillance sampling will be performed by the study protocol nurse on daily ward rounds during week days, by collecting swabs of nares, throat, perineum, and any wound, bladder or intravenous catheter exit site and endotracheal aspirate in ventilated patients for conventional selective MRSA culture (see appendix 1). For the denominator, a patient will be counted as two ward admissions if staying outside the ward for more than 24 h.

All isolates will be saved at -80°C for typing of relevant isolates to identify transmission clusters. Genotyping will be performed by *spa* sequence analysis and SCC*mec* typing (see appendix 5 for MRSA typing procedure).

Interim analysis and contingency plan.

After the first 10 weeks of the 3-month baseline period, 2 weeks will be used to analyse data and check ward eligibility based on fulfillment of the following “pass criteria”:

(1) > 80 % compliance with admission and discharge conventional culture screening, calculated for weeks 8-10 for the pooled admissions to all study wards;

(2) > 80 % compliance with additional MRSA contact isolation procedures, calculated for weeks 8-10 based on a sample of observations of 50 patient care contacts per hospital in all study wards;

(3) pooled incidence of nosocomial MRSA acquisition ≥ 3 new cases /100 at risk admissions in the study wards for weeks 1-10.

These criteria must be met for each hospital to ensure sufficient compliance with the protocol, a sufficient denominator of exposed number of patients per month in the study wards and target incidence figures. If either of these pass criteria is not fulfilled, the two trial phases can be extended to 6 or 7 months and/or further compliance reinforcement will be undertaken before starting the randomisation of units for inclusion in the intervention phase.

In addition, MRSA isolates will be typed to ensure that no atypical SCC*mec* variants are emerging.

In case of outbreak of MRSA or other infections detected at any time during the study, additional contingency outbreak control interventions may be decided by the hospital’s Infection Control Committee. These non-protocol interventions, if any, will be recorded, described in the final report and taken into account at analysis stage.

**Study endpoints and statistical analysis**

The **primary endpoint** of the study will be the following microbiologically documented outcome:

1. **Incidence density rate of MRSA nosocomial colonisation**, defined as the number of new cases of hospital-acquired MRSA (first positive culture > 48 h after admission) divided by the number of patient days at risk (defined as cumulated lengths of stay by patients who stayed ≥ 3 days and were MRSA negative on admission screening by conventional culture, and, if performed, PCR test).

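### The numerator of the primary endpoint is not restricted to the population in its denominator, so patients with no at-risk time can count as hospital-acquired cases

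*Protocol*

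**What the plan says.** Under Study endpoints and statistical analysis, the primary endpoint is the number of new hospital-acquired cases ("first positive culture > 48 h after admission) divided by the number of patient days at risk"). The denominator is the summed stay of "patients who stayed ≥ 3 days and were MRSA negative on admission screening by conventional culture, and, if performed, PCR test". The cumulative-incidence endpoint, listed under Secondary endpoints, pairs its numerator and denominator in the same way.

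Three other statements decide who can become a case:

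- **Admission sampling.** In the intervention arm, "all patients admitted to study wards will be sampled within 24 h after admission"; the control arm has the same 24 h limit. PCR is added in the intervention arm only.
- **Discharge sampling.** Under Primary outcome monitoring and case finding procedures, "active discharge surveillance will be performed in all patients who have stayed in study wards for more than 48 h". Admission-screen status is not a condition.
- **Compliance.** The pass criterion for the baseline phase is more than "80 % compliance with admission and discharge conventional culture screening". Addendum 1 reports that admission screening exceeded 80% and that discharge screening reached 68%.

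**The concern.** A rate is interpretable only if every counted event comes from someone whose time is in the denominator. Here a case is fixed by the timing of the first positive culture alone, whereas time at risk also requires a negative admission screen and a minimum stay. A carrier who was not cultured on admission and is first cultured at discharge meets the written case definition, although the carriage was imported.

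The trial is built to detect a halving of acquisition. Addendum 1 found baseline incidence far below plan and claims 80% power only with both hospitals pooled and at the upper confidence limit of that incidence. With so few true acquisitions, a modest number of imported cases in both arms could move the estimated ratio noticeably. The trial is also open label, so the decision to keep or drop such cases should not be left until the data are seen.

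**Working it through.** **1. Who can be a case without at-risk time**

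| Patient | Meets written case definition? | In denominator? |
| --- | --- | --- |
| Screened, culture-positive on admission | No: positive within about 24 h | No |
| Screened, false-negative culture, positive later (no positive PCR) | Yes | Yes |
| No admission culture, positive at discharge | Yes | No |
| PCR-positive, culture-negative on admission, culture-positive later (intervention arm only) | Yes | No |
| Stay > 48 h but < 3 days, positive after 48 h | Yes | Depends on how days are counted |

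The mismatch lies in the third and fourth rows, and possibly the fifth.

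**2. The plan's own figure**

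Sample size estimate gives 1,237 per arm for 3% versus 1.5%, α = 0.05, 80% power. With Poisson variances and one-sided α:

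(1.6449 + 0.8416)² × (0.03 + 0.015) / 0.015² = 6.1827 × 200 = 1,236.5, i.e. 1,237.

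Multiplying by 1.5 gives about 1,856, which the plan rounds to 1,850. The same calculation two-sided gives 1,570; the plan does not state sidedness. Pooled, there are 3,700 per arm, or 3,700 / 1.5 = 2,467 effective. At 1.55% versus 0.775%, one-sided power is 0.81, in line with Addendum 1.

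**3. Effect of unscreened carriers on the ratio**

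Inputs:
- control acquisition *a* = 1.55 or 0.79 per 100 (Addendum 1, upper limit and point estimate)
- true ratio 0.50
- unscreened share 20% (the most the criterion allows)
- discharge detection 68% (Addendum 1)
- previously unrecorded carriage on admission 2%, 5% or 10% (**assumed; not in the Protocol**)
- the added cases are taken as equal in both arms (**assumed**)

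Added cases per 100: *m* = 100 × 0.20 × carriage × 0.68 = 0.272, 0.68 or 1.36.

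Apparent ratio = (0.5*a* + *m*) / (*a* + *m*).

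| Carriage | *a* = 1.55 | *a* = 0.79 |
| --- | --- | --- |
| 2% | 1.047 / 1.822 = 0.57 | 0.667 / 1.062 = 0.63 |
| 5% | 1.455 / 2.230 = 0.65 | 1.075 / 1.470 = 0.73 |
| 10% | 2.135 / 2.910 = 0.73 | 1.755 / 2.150 = 0.82 |

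With 10% unscreened, the ratios at *a* = 1.55 are 0.54, 0.59 and 0.65.

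One-sided pooled power at 1.55% falls from 0.81 to 0.74, 0.65 and 0.54 for the three carriage values with 20% unscreened. Two-sided, it falls from 0.72 to 0.63, 0.53 and 0.41.

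**4. The one-arm PCR exclusion**

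Take 5% carriage, 5% of carriers with a false-negative culture (the Protocol's introduction cites 95-100% culture sensitivity), and assume all are found later. Imported cases are 5 × 0.05 = 0.25 per 100. At *a* = 1.55:

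- None excluded in either arm: (0.775 + 0.25) / (1.55 + 0.25) = 0.57.
- PCR excludes all of them from the numerator, intervention arm only: 0.775 / 1.80 = 0.43.
- The same exclusion with no true effect: 1.55 / 1.80 = 0.86.

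Confining the numerator to patients negative on culture *and* PCR could therefore favour the intervention. Under the written numerator, the same patients' later positive cultures count as intervention cases without person-time, which pushes the other way.

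**The case against.** The strongest reply is that the stated analysis already resolves this. The primary model is a two-level Poisson regression with an individual-patient level, and the rate ratio is reported for the at-risk population. A patient with no at-risk days has no exposure and would probably drop out. This has force: the documents do not show that such cases would be analysed, so the mismatch is not proof of a biased result. But the Protocol never says they are dropped, and its literal endpoint definition counts them. The definition and the model disagree on a point the Protocol itself fixes.

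A second reply is that the size is unsupported. This largely stands. Admission carriage is not given, 20% is a ceiling rather than a measured share, and daily rounds check admission screening. It is also unclear whether the 0.79% already contains imported cases. At 10% carriage, *m* = 1.36 would exceed the whole measured 0.79, though not its upper limit of 1.55. If 0.79 does include them, dilution is larger. At 2% carriage, true acquisition would be 0.79 − 0.272 = 0.518 and the ratio (0.259 + 0.272) / 0.79 = 0.67 instead of 0.63.

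Three stronger readings are tempting but not supported:

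- *That dilution is certain.* It rests on similar non-screening in both arms, and the PCR exclusion acts in one arm only.
- *That carriers with a false-negative admission culture are part of this defect.* With no positive PCR they are in both numerator and denominator.
- *That discharge swabs, allowed up to 72 h before discharge, create false cases in short stays.* A positive culture before 48 h is already excluded by the case definition.

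**Conclusion.** The point holds as a defect of definition in the primary endpoint and the cumulative-incidence endpoint: as written, patients outside the at-risk population can supply events. The groups clearly affected are patients without an admission culture and intervention-arm patients who were PCR-positive but culture-negative. Stays between 48 h and 3 days may be affected too; if admission is counted as day 1, that gap may vanish.

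The likely direction for unscreened carriers is towards a ratio of 1, provided non-screening is similar between arms. The illustrative ranges are 0.57-0.73 at a 1.55% control rate and 0.63-0.82 at 0.79%, for a true ratio of 0.50. They depend on the assumed 2-10% carriage and the 20% ceiling and are not estimates for this trial. The PCR-based exclusion has no fixed direction. The definition should be corrected because it governs the primary result and Addendum 1 leaves little power to spare.

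**What to change.** Define one at-risk cohort and use it for both numerator and denominator:

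- **Cohort:** admission culture taken and negative, a criterion available in both arms, with one stay threshold replacing the mix of > 48 h and ≥ 3 days.
- **Case:** a member of that cohort whose first positive culture is more than 48 h after ward admission.
- **Separate table by arm:** late positives without a negative admission culture.
- **Sensitivity analysis:** exclude patients who were PCR-positive on admission, noting that this can be done in one arm only.
- **Same rule** for the cumulative-incidence endpoint and its logistic model.

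The cost is about one sentence per endpoint; the plan already collects the admission times and culture results needed. The downside is that some events leave the primary count, including true acquisitions in unscreened patients. In step 3, removing the unscreened cases returns the ratio to 0.50 and one-sided power at 1.55% to 0.81, provided the planned 3,700 per arm are all in the cohort. The fix does not remove carriers with a false-negative admission culture, who remain in both numerator and denominator.

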The **primary analysis** will be based on Poisson regression two level model (individual patient and unit exposure) performed at each hospital level to assess the impact of the intervention on local incidence-density of MRSA nosocomial colonisation, and ajusted for four potentially confounding factors. The dependent variable will be endpoint 1 above. The ward level **independent variables** will include (1) **intervention arm**, (2) MRSA **colonisation pressure** (as determined by monthly proportion of MRSA colonisation-days/total patient-days among patients admitted during the preceding month in one particular ward), (3) **staff** **compliance with standard and isolation precautions** (as determined by a sample of 50 observations per ward/ trial period, including 25 care opportunities for patients under MRSA isolation precautions and 25 for patients cared for with standard precautions; see appendix 6 for precautions compliance monitoring procedure) (4) **antibiotic use** (as determined by cumulated number of Defined Daily Doses of J01 ATC class of antimicrobial drugs per monthly period) and (5) monthly bed occupancy rate.

Heterogeneity of effect by ward/hospital will be assessed. **To quantify the protective efficacy of the intervention** for the at risk population per centre, the adjusted Rate Ratio (and 95% confidence interval) of nosocomial MRSA acquisition will be calculated for the intervention arm in all study wards per hospital. Pooled analysis of average effect for both hospitals will be calculated. In case of significant heterogeneity between hospitals, hospital level will be added as covariate in the model.

**Secondary analyses** will include:

A. Logistic regression two level models (individual patient and unit exposure) will be performed at each hospital level to assess the impact of the intervention on local cumulated incidence of MRSA nosocomial colonisation. The dependent variable will be endpoint 6 above. The **independent variables** will include patient age, sex and the 5 independent ward level indicators as described above for the primary Poisson analysis.

Heterogeneity of effect by ward/hospital will be assessed. Pooled analysis of average effect for both hospitals will be calculated. In case of significant heterogeneity between hospitals, hospital level will be added as covariate in the model.

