**Sample size estimate.**

Based on the cumulated incidence endpoint and study hypothesis that shortening time to detection of MRSA carriage by 3 days will reduce MRSA nosocomial acquisition by 50%, a standard sample size calculation for detecting a difference in proportion between 3% and 1.5% in two independent samples with α=0.05 and ß=0.20 (80 % power) suggests that 1,237 patients should be included in each study arm. Assuming non-independence of samples due to the time dependence of MRSA transmission rates between study phases and taking into account the cluster design, a conservative 150 % sample size estimate would suggest enrollment of 1850 patients per arm in each hospital, or a total inclusion of 7,400 patients.

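### The primary endpoint's days at risk include days after MRSA has been acquired: a minor error of definition that can pull the rate ratio slightly towards 1

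*Protocol*

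**What the plan says.** The primary endpoint is set out in the protocol under *Study endpoints and statistical analysis*. It is an incidence density, with these parts:

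- Numerator: "defined as the number of new cases of hospital-acquired MRSA (first positive culture > 48 h after admission").
- Denominator: "number of patient days at risk (defined as cumulated lengths of stay by patients who stayed ≥ 3 days" and who "were MRSA negative on admission screening by conventional culture, and, if performed, PCR test").

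MRSA status enters the denominator only at admission. The one further denominator rule is under *Primary outcome monitoring and case finding procedures*: "For the denominator, a patient will be counted as two ward admissions if staying outside the ward for more than 24 h". It concerns absence from the ward, not acquisition. The same paragraph has discharge cultures taken "either on the day of being discharged or within 72 h prior to discharge from the study ward".

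The primary analysis "will be based on Poisson regression two level model (individual patient and unit exposure"), with this endpoint as the dependent variable. It does not restate the exposure. Addendum 1 makes the pooled result of both hospitals primary and leaves the denominator as it was. Addendum 2 only adds a wash-out month.

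**The concern.** Days at risk should be days on which a patient can still become a case. Because the numerator takes only the first positive culture, risk ends there. Cumulated length of stay does not end there, so a patient who acquires MRSA goes on adding days to the denominator until discharge.

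Two other parts of the protocol show the inconsistency:

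- The primary model adjusts for colonisation pressure, built from MRSA colonisation-days over total patient-days. A day after a positive culture can count as colonised in that covariate and as susceptible in the outcome.
- A patient who acquires MRSA, leaves the ward for more than 24 h and returns still positive starts a new admission that fails the admission-negative condition, so those days drop out. A patient who acquires MRSA and stays on the ward keeps contributing days. The same colonisation is treated differently according to ward movement.

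At stake is the primary rate ratio. The surplus days grow with the number of cases, so with similar stay after detection they lower the rate more in the arm with more acquisitions. The reported rates also come to depend on how long cases remain after detection, which is not a measure of acquisition risk.

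**Working it through.** **The plan's own figure.** The sample size rests on cumulative incidence: a "difference in proportion between 3% and 1.5% in two independent samples with α=0.05 and ß=0.20 (80 % power"), which "suggests that 1,237 patients should be included in each study arm". A one-sided 5% comparison with Poisson variance reproduces this: (1.645 + 0.842)² × (0.03 + 0.015) / 0.015² = 1,236.5. The protocol does not state sidedness; that is a separate matter. The calculation counts patients and not days, so the present point leaves it unchanged.

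**Inputs from the protocol.** Planned control incidence p = 0.03, with a 50% reduction. Baseline incidence 0.79% (Addendum 1). Planned enrolment of 1,850 per arm per hospital, hence 3,700 per arm pooled.

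**Assumptions.** The protocol gives neither quantity below.

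- L, mean at-risk days per stay: 8–10.
- d, mean days in hospital after first positive culture. The design section expects pre-discharge screening to double detection, so about half of cases would be found by it. Those have 0–3 later days, given the 72 h window. The other half are given 5–15 days. The mean runs from (0 + 5)/2 = 2.5 to (3 + 15)/2 = 9.

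**Formula.** With days ended at detection, each patient contributes L days on average. With the full stay, the control arm contributes L + p·d per patient and the intervention arm L + (p/2)·d. A true ratio of 0.500 is then observed as

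0.5 × (L + p·d) / (L + (p/2)·d).

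**Results.**

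| p | L, d | Calculation | Ratio reads | Control denominator too large by p·d/L |
|---|---|---|---|---|
| 3% | 10, 2.5 | 0.5 × 10.075/10.0375 | 0.502 | 0.75% |
| 3% | 8, 9 | 0.5 × 8.27/8.135 | 0.508 | 3.4% |
| 0.79% | 10, 2.5 | 0.5 × 10.01975/10.009875 | 0.5005 | 0.20% |
| 0.79% | 8, 9 | 0.5 × 8.0711/8.03555 | 0.502 | 0.89% |

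**Direction.** The relative surplus is p·d/L in the control arm and (p/2)·d/L in the intervention arm when d is the same in both. If d differs, the direction at a true ratio of 0.5 reverses only when intervention-arm cases stay more than twice as long after detection. If the arms have equal incidence and similar stays, the surpluses are equal and there is no bias.

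**Against random error.** At 0.79%, 3,700 per arm gives 29.2 control cases and, at half the rate, 14.6. SE(log ratio) = √(1/29.2 + 1/14.6) = 0.32. The 95% interval around 0.50 is about 0.27–0.94 before any allowance for clustering.

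**The case against.** **The effect is negligible.** At the baseline incidence the ratio moves by about 0.002 at most, against an interval of 0.27–0.94. When the arms have similar stays after detection, the shift is towards no effect and cannot create a false benefit. This stands, and it is why the point is minor.

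**Another planned analysis is immune.** The cumulative-incidence endpoint, analysed by two-level logistic regression, counts patients. True, but that endpoint is secondary; the primary one still carries the error.

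**Exposure handling belongs in the SAP, and the phrase 'at risk' already implies stopping at the event.** Only the label implies it. The protocol goes on to give an explicit definition that says otherwise. An SAP that followed it would carry the error forward, and one that stopped at the event would depart from it.

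**Stopping at the first positive culture does not yield exact risk time.** This stands. With cultures mainly at admission and discharge, the first positive is a detection date, and days between acquisition and detection remain counted. The first 48 h of each stay, when no case can be counted, also remain: about 2 of the assumed 8–10 days. In principle that portion does not differ by arm.

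**Stronger readings that the protocol does not support.** A reader might give every case 5–15 later days and obtain 0.504–0.514 at 3%, or 0.501–0.504 at 0.79%. That overlooks discharge screening, which leaves few later days for many cases. Its top figure also pairs the shortest assumed stay with the longest time after detection, although wards with long stays raise both. A reader might also infer that the bias always runs one way; this depends on similar stay after detection in the two arms.

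**Conclusion.** The definition is wrong as written, and the correction is minor. The denominator is called days at risk but counts the full stay of every eligible patient, including days after that patient has become a case.

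If stay after detection per case is similar in both arms and PCR reduces acquisition, the primary rate ratio is drawn slightly towards 1. A true 0.500 reads about 0.502–0.508 at 3% incidence and about 0.5005–0.502 at 0.79%. These ranges rest on the assumed stays; only the ratio d/L and the incidence matter. The protocol gives no ground for saying that the error threatens the trial's conclusion or could produce an apparent benefit where none exists when stays are similar.

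**What to change.** In the primary endpoint definition under *Study endpoints and statistical analysis*, keep the existing eligibility conditions. Add that an eligible patient's days at risk end at the earliest of first MRSA-positive culture, ward discharge or death. In the primary analysis paragraph, name these days as the Poisson exposure.

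State beside it that the first positive culture is a detection date, so days between acquisition and detection remain in the denominator.

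Leave the colonisation-pressure covariate as defined. Days after detection belong in both its numerator and its total patient-days; moving them to the numerator alone would distort the covariate.

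The cost is a sentence or two. No new data collection appears necessary, since the laboratory information system already records sample reception and result notification times. Reported rates rise slightly, and no sample-size figure changes.
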